### 3.8. Sample Size

This sample size considers a loss at follow-up of 20% of the students. Considering a 20% of school rejection at the recruitment stage, we expect to recruit 12 schools. Studies of similar school-based interventions report effect sizes of at least 0.4 standard deviation using symptoms questionnaires as proposed here [71]. We used the results previously observed by Hetrick et al. [49] and the clustersampsi command in Stata Software to estimate the number of clusters in two arms, using the following command: clustersampsi, samplesize mu1(X1) mu2(X2) sd1(Y1) sd2(Y27) m(Z) rho(R). Where X1 = mean in arm 1; X2 = mean in arm 2; Y1 = standard deviation (SD) in arm 1; Y2 = SD in arm 2; Z = number of children per school on average (harmonic mean) (*n* = 14); and R = intracluster correlation. The two arms will be balanced for school size. 

### 3.9. Recruitment

The strategies for achieving adequate school enrolment to reach the target sample size will include contacting, and presenting the study to, municipality authorities, who are expected to help to establish contact with school authorities. Additionally, research assistants will contact directly and inform school authorities about the purpose, requirements, and duration of the study. Our research team already has good collaborative networks with municipalities and schools in the cities where the study will be conducted.

## 4. Assignment of Interventions: Allocation

Randomization will be performed once all schools are recruited. Schools will be randomly assigned to either group with a 1:1 allocation as per computer-generated randomization. In order to reduce the risk of allocation bias, the size of the schools and the vulnerability index will be taken into account to balance the groups. 

### 4.1. Sequence Generation

Randomization will be performed once all schools are recruited. Schools will be randomly assigned to either group with a 1:1 allocation as per computer-generated randomization.

### 4.2. Concealment Mechanism

After the randomization and allocation, schools will be informed by a research assistant of the group of belonging by email and confirmed by telephone. Each school will only receive their information of allocation. Additionally, this information will not be disclosed to the assessment research team (outcome evaluators) to keep the blind to the school allocation.

### 4.3. Allocation Implementation

An independent statistician will perform the randomization to assign to the study arms. This statistician will give this information to a research assistant. Later, the research assistant will inform the schools by email and confirm by telephone.

## 5. Assignment of Interventions: Blinding

### 5.1. Who Will Be Blinded?

This is a double-blinded trial, blinded to the outcome evaluators and to the data analyst. Outcome evaluators will not be informed about the group of belonging and will be instructed not to ask for the school condition to the students nor to the school authorities. A data analyst will work with the final dataset, where the group condition will be masked.

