### 1.3. Trial Design

This is a protocol for a single-blind, two-armed randomized controlled trial evaluating changes in primary and secondary outcomes post-intervention and follow-up. The two arms will be: (a) the intervention, which comprises eight internet-based modules of CBT delivered over 10-weeks using the program Reframe-IT and four 45-min face-to-face psychotherapeutic CBT sessions, and (b) control group (Treatment-As-Usual) (see Table 1).

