### 3.4. Strategies to Improve Adherence to Interventions

Adherence to the intervention will be monitored by research assistants from the research team. School psychologists will fill out a small survey after each session informing the attendance of students and information about the quality of the delivery. Research assistants will be in close contact with school authorities and school psychologists, monitoring the progression of the program during study visits.

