### 5.2. Procedure of Unblinding If Needed

The design is open-label with only outcome assessors and data analysts being blinded, so unblinding will not occur. Additionally, by the nature of the intervention, the participants are not blind to the group in which they belong. The evaluations will be carried out through self-report questionnaires sent in electronic format and their evaluation will be automatic without human action. In data analysis, the statistician will be blind to the intervention group of participants.

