### 7.4. Methods in Analysis to Handle Protocol Non-Adherence and Any Statistical Methods to Handle Missing Data

The primary outcome will be assessed using an intention-to-treat analysis. Missing data will be reduced to a minimum by using the appropriate measures; encouraging students to fill out the whole questionnaire, a research assistant will revise the questionnaire when students end the evaluation and ask to complete the instruments if some questions are unanswered. Multiple imputations will be used to handle missing data in the primary and secondary analyses.

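### The trial is called double-blinded, single-blind and open-label in different sections, and blinding of outcome evaluators does not protect a primary outcome that unblinded students report themselves

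*Protocol article*

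**What the plan says.** The article describes blinding in four places. The abstract says single-blind, and Section 1.3 repeats it: "single-blind, two-armed randomized controlled trial". Section 5.1 says: "This is a double-blinded trial, blinded to the outcome evaluators and to the data analyst". Section 5.2, which follows directly, says: "The design is open-label with only outcome assessors and data analysts being blinded". It adds that participants know their group because of the nature of the intervention.

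On measurement, Section 3.6.1 defines the primary outcome as the SIQ, a 15-item self-report scale, and Section 3.6 has it collected electronically in Qualtrics. Section 5.2 says of the self-report questionnaires that "their evaluation will be automatic without human action". Section 7.4, on missing data, says that "a research assistant will revise the questionnaire when students end the evaluation and ask to complete the instruments" where questions are unanswered.

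On staff roles, Section 4.2 withholds allocation from the assessment team, and Section 5.1 tells evaluators not to ask students or school authorities about it. Section 4.3 says of the randomization result: "This statistician will give this information to a research assistant", who then informs the schools. Section 3.4 says: "Adherence to the intervention will be monitored by research assistants from the research team".

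**The concern.** Readers use the blinding statement to judge how far measurement of the outcome could depend on treatment arm. For a subjective outcome such as suicidal ideation, double-blinded with blinded evaluators suggests that the ratings were made without knowledge of the arm. Here the rating is made by the student, who knows the arm.

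The second issue is the human step in Section 7.4. When a student finishes, an assistant goes over the questionnaire and may ask for more answers. If that person knows the arm, or is familiar to students in intervention schools from adherence monitoring, answers to sensitive items could be influenced differently in the two arms. Masking the analyst would not correct this, because any difference would already be in the data.

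**Working it through.** No arithmetic applies, and the plan gives no figure to reproduce. The check sets the statements side by side.

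**1. The labels.**
- Abstract and Section 1.3: single-blind.
- Section 5.1: double-blinded, explained as evaluators and data analyst.
- Section 5.2: open-label, with only assessors and analysts blinded, and participants not blind.

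Sections 5.1 and 5.2 name the same two blinded parties, so they agree on who is blinded. They differ on what to call it, and neither label matches the abstract and Section 1.3. This is three names for one design, and condensing a longer protocol into an article does not explain it.

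**2. What each safeguard protects, for the primary outcome.**
- The student answers the SIQ (Section 3.6.1) and is unblinded (Section 5.2).
- Scoring is automatic (Section 5.2), so no evaluator exercises judgement on the score. Keeping allocation from evaluators therefore protects no rating of the SIQ.
- The analyst works on a dataset with the group masked (Section 5.1). This guards against choices in the analysis that depend on arm. It does not affect how students answered.

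**3. Automatic evaluation against the completeness check.** Section 5.2 excludes human action. Section 7.4 puts an assistant between the student's first submission and the final answers. Section 6.2 adds that researchers check responses during follow-up and contact schools and participants where needed. If Section 5.2 refers only to scoring, the sections are compatible, but the article does not say so.

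**4. Who does the check.** At least one research assistant knows the allocation (Sections 4.2 and 4.3). Research assistants monitor adherence to the intervention, including during study visits (Section 3.4). The assessment team is not told the allocation (Section 4.2). Section 7.4 says only that a research assistant does the check, without placing that person in either group. The text allows both a blinded and an unblinded checker.

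**The case against.** The strongest reply is that nothing is hidden. Section 5.2 says plainly that participants are not blind and that the questionnaires are self-reported, and Section 5.1 explains its label in the same sentence. Unblinded self-report is hard to avoid in a trial of psychotherapy. This stands: the fault lies in the labels and in the protection they imply, not in concealment.

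A reader might infer that the Section 7.4 assistant is unblinded. The documents do not support that. Section 4.2 names an assessment team from whom allocation is withheld, Section 5.1 forbids evaluators to ask, and nothing says that the assistant who announces allocation or those who monitor adherence also check questionnaires. The text describes prompting for blanks, not discussing the content of answers. What remains is that the role is not assigned.

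A reader might also infer that blinding of staff is irrelevant to every outcome because all are self-reported. That goes too far. Section 3.6.2 lists adherence to usual-care actions, which a research assistant registers, so withholding allocation from staff may still have value there.

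Finally, the in-person check is a deliberate safeguard against missing data, and removing it could cost some completeness. That is a fair point and bears on the choice of fix.

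**Conclusion.** The point holds in a limited form. Double-blinded is a property that this design lacks, and it conflicts with the article's other descriptions. Evaluator blinding does not protect measurement of the primary SIQ; analyst masking is genuine but acts at a different stage. Both conclusions follow from the text.

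The conclusion on Section 7.4 is weaker: an unassigned role and wording that fits poorly with Section 5.2 leave open an avoidable route to arm-dependent answers. Whether that route is used depends on who does the check, which the article does not say.

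No size can be given. The documents contain nothing from which the amount or direction of a reporting difference between arms could be derived. A reader might infer that the primary result is invalid; the documents do not support that. The trial remains interpretable as an open-label trial with self-reported outcomes, provided that it is described as one.

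**What to change.** - **Abstract and Sections 1.3, 5.1 and 5.2:** use one description: open-label for students and schools, self-reported outcomes rated by unblinded participants, assessment staff not told the allocation, analyst masked. Drop double-blinded. Keep the commitment to withhold allocation from assessment staff, without presenting it as protection for the SIQ.
- **Section 7.4:** replace the assistant's check with an automatic prompt for unanswered items in Qualtrics, which already collects the data. Alternatively, keep the check but restrict it to assessment-team members with no part in announcing allocation or monitoring adherence.
- **Section 5.2:** align the sentence on automatic evaluation with whichever option is chosen, for example by stating that it refers to scoring.

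The cost is wording plus either a survey setting or a rule on staff roles. The blinding statement becomes less favourable, and questionnaires may be slightly less complete if the in-person check is dropped. Keeping the check within the assessment team avoids that second cost. The endpoint, sample size and intervention do not change.

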### 5.2. Procedure of Unblinding If Needed

The design is open-label with only outcome assessors and data analysts being blinded, so unblinding will not occur. Additionally, by the nature of the intervention, the participants are not blind to the group in which they belong. The evaluations will be carried out through self-report questionnaires sent in electronic format and their evaluation will be automatic without human action. In data analysis, the statistician will be blind to the intervention group of participants.

## 6. Data Collection and Management

### 6.1. Plans for Assessment and Collection of Outcomes

Self-report questionnaires assessing primary and secondary outcomes will be administered at baseline (one week before the start of the intervention), at post-intervention, and follow-up (3, 6, and 12 months). Primary and secondary outcomes will be measured electronically using Qualtrics. 

### 6.2. Plans to Promote Participant Retention and Complete Follow-Up

The schools, students, and their families will receive extensive information about the study setup and requirements during the recruitment. This information will include and stress the importance of completion of follow-up. From the start of the implementation of the assessments, students will be reminded of the value of their active participation during the whole project. Throughout the follow-up period, the researchers will check responses and if necessary contact schools and participants for completion of their follow-up. 

### 6.3. Data Management

After the participants have completed the online questionnaires, we will enter the data into a secure platform without identifying information (each participant will be assigned an encrypted ID number). Only the principal investigator, the research assistants in charge of data entry, and the statistician will have access to the database. All people with access to the dataset will need to sign a confidential agreement to assure the commitment to not revealing identifying information.

## 7. Statistical Methods

### 7.1. Statistical Methods for Primary and Secondary Outcomes

We will use descriptive statistics to assess balance across arms at baseline. The primary between-group analysis will be carried out on an intention-to-treat basis for 3-month SIQ scores. We will use linear mixed effects model analysis to compare the intervention and control groups regarding the change in outcome measures from baseline to post-intervention and the follow-up time point. The school is included as a random factor for each outcome measure to account for possible school effect. We will use Fisher’s exact test to compare the frequency of suicide attempt cases between groups. We also will conduct a Complier Average Causal Effect (CACE) analysis to assess the impact of the number of sessions on the primary outcome. All analyses will be performed using STATA 15.01. 

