## Abstract

Suicidal ideation is prevalent in adolescents and is a marker for subsequent psychiatric vulnerability and symptom severity. Literature shows that blended care (integrating online and offline components in a treatment process) could improve the effectiveness and adherence of interventions targeting suicidal ideation in adolescents, but the evidence is inconclusive. Thus, we will test the effectiveness of a blended intervention to reduce suicidal ideation (primary outcome) in school settings using a single-blind two-armed cluster randomized controlled trial (cRCT). The internet-based component corresponds to the Reframe-IT, a program encompassing eight online sessions based on cognitive-behavioral therapy (CBT) principles. The face-to-face intervention will be delivered through four CBT sessions. Additionally, we will assess the effect of the intervention on the following secondary outcomes: suicidal attempts, depressive symptoms, hopelessness, emotional regulation, and problem-solving skills. Primary and secondary outcomes will be assessed at post-intervention, 3-month, 6-month, and 12-month follow-up. Finally, we will explore the mediation role of cognitive, emotional, and behavioral correlates of suicide on the effect of the intervention. Results will inform whether the intervention can reduce suicide among school adolescents and be implemented on a large scale in Chile.

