### 2.1. Study Setting

Participants will be adolescents attending schools with secondary education (grades 9–11), mixed sex, located in three different cities in the South of Chile, with at least two classes per year. We expect to recruit at least ten schools per arm. Each arm should include 140 eligible students.

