#### 3.6.2. Secondary Outcomes and Questionnaires

Suicide attempt: two questions assessing whether participants had attempted suicide; if yes, how many attempts?

Anxiety as trait and as state: The State–Trait Anxiety Inventory (STAI-X) [65] is a self-report questionnaire with two scales of 20 items, each assessing state and trait levels of anxiety. Respondents indicate how they generally feel on a 4-point Likert scale from 0 (almost never) to 3 (almost always). The minimum score is 0 and the maximum score is 60 for both scales. Higher scores mean higher trait or state anxiety levels. It has been validated in the Chilean population aged 13–60 years old [66].

Hopelessness: The Beck Hopelessness Scale [67] is a self-report scale with 20 true or false items, nine of which are keyed ‘false’ and 11 are keyed ‘true’. For every statement, each response is assigned a score of 0 or 1 and the total hopelessness score is the sum of the scores on the individual items. The minimum score is 0 and the maximum score is 20. A higher score means higher hopelessness levels.

Social problem solving: The short form of the Social Problem-Solving Inventory Revised (SPSI-R Short Form) [68] is a 25-item self-report instrument measuring two adaptive problem-solving dimensions (positive problem orientation and rational problem solving) and three dysfunctional dimensions (negative problem orientation, impulsivity/carelessness style, and avoidance style). Each item is rated on a 5-point scale ranging from ‘not at all true of me’ (0) to ‘extremely true of me’ (4). The minimum score is 0 and the maximum score is 75. A higher score means a higher social problem-solving capability.

Cognitive-behavioral skills: The Cognitive-Behavioral Therapy Skills Questionnaire (CBTS) [69] is a 16-item scale with two scales measuring two skills: cognitive restructuring (CR) and behavioral activation (BA). Respondents rank each item on a 5-point Likert scale from 1 (I don’t do this) to 5 (I always do this). The minimum score is 15 and the maximum score is 80. A higher score means a higher presence of cognitive-behavioral skills. To assess general CBT skills, we have removed those items that refer exclusively to the practice of CBT sessions (e.g., keep track of the signs and symptoms of my condition); therefore, general CBT skills could be assessed before and after the intervention in both groups. 

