### 7.2. Statistical Methods for Additional Analyses

We will fit multilevel multiple mediation models in Mplus 6 [72], entering all hypothesized mediators simultaneously [73]. The conceptual model of mediation is depicted in Figure 1. 

We will calculate the intervention effect for each mediator, the effect of each mediator on the outcome (suicidal ideation), and the intervention effect that was mediated by each mediator. For each model, we will compute the total indirect effects of the intervention (i.e., the total effect of intervention mediated by the sum of the mediating factors) and the single indirect effect for each mediator as suggested by Preacher and Hayes [73]. Moreover, we will calculate the program’s direct effect (i.e., the effect not explained by the hypothesized mediators). The randomization occurred at the school level; therefore, we will enter school as the second level and individuals as the first level. To control for variability across schools, we will use the stratification option in Mplus. 

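### Suicide attempts are to be compared with a student-level Fisher's exact test although schools are randomised, so the p-value is too small to the extent that attempts correlate within schools

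*Protocol article*

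**What the plan says.** The unit of randomisation is the school. Section 4.1: "Schools will be randomly assigned to either group with a 1:1 allocation as per computer-generated randomization". Section 4 adds that school size and a vulnerability index are used to balance the arms.

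The outcome is recorded per student. Section 3.6.2: "Suicide attempt: two questions assessing whether participants had attempted suicide", with a follow-up question on how many. The Abstract puts it first among the secondary outcomes: "suicidal attempts, depressive symptoms, hopelessness, emotional regulation, and problem-solving skills".

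Section 7.1 assigns this outcome to Fisher's "exact test to compare the frequency of suicide attempt cases between groups". It names no cluster-level test, design-effect correction or logistic mixed model for it.

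Elsewhere the protocol does allow for school. In Section 7.1, directly after the linear mixed model is introduced: "The school is included as a random factor for each outcome measure to account for possible school effect". In Section 7.2, for mediation: "The randomization occurred at the school level; therefore, we will enter school as the second level and individuals as the first level".

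On size, Section 2.1 says "We expect to recruit at least ten schools per arm" and "Each arm should include 140 eligible students". Section 3.8 gives an average of 14 students per school and a 20% loss to follow-up. It expects 12 schools, without saying whether per arm or in total, and shows the ICC only as a symbol.

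**The concern.** Fisher's test on a two-by-two table of students takes every student as an independent observation. When schools are randomised, any tendency of attempts to occur together within schools makes the difference between arms vary by chance more than the test allows. A cluster of attempts in one or two schools could then be read as evidence of benefit or harm.

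The protocol's own reasoning points the other way: Section 7.2 derives the need for a school level from the unit of randomisation, and that argument applies equally to attempts. This is also the gravest of the listed outcomes, and a between-arm p-value for it will be noticed even though it is secondary.

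**Working it through.** **Inputs from the protocol article.** Schools are randomised 1:1 (4.1). There are at least 10 schools and 140 students per arm (2.1), 14 students per school and 20% loss (3.8). The planned size is consistent with itself: 10 × 14 = 140 per arm. The protocol states no significance level, event rate or error rate for the attempt comparison, so there is no figure of its own to reproduce.

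**Assumptions.** Two-sided 5% level; ICC 0 to 0.10; attempt risk 3% to 20%, equal in both arms.

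**Step 1: design effect.** DE = 1 + (m − 1) × ICC with m = 14, and effective students per arm = 140 / DE. For a large-sample test that ignores clustering, the true error is 2 × [1 − Φ(1.96 / √DE)].

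| ICC | DE | Effective n per arm | Large-sample error |
|---|---|---|---|
| 0.01 | 1.13 | 124 | 6.5% |
| 0.02 | 1.26 | 111 | 8.1% |
| 0.05 | 1.65 | 85 | 12.7% |
| 0.10 | 2.30 | 61 | 19.6% |

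**Step 2: Fisher's test itself.** Fisher's test is conservative when events are few, so Step 1 overstates the problem for it. A null simulation is needed: school risks drawn from a beta distribution with the given mean and ICC, binomial counts within schools, and 20,000 trials per setting. The ranges below run over attempt risks of 3% to 20%.

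| ICC | Fisher, 10 schools × 14 per arm | t test on school proportions, same design |
|---|---|---|
| 0 | 2.0–3.5% | 4.5–5.0% |
| 0.01 | 2.4–4.8% | 4.0–5.1% |
| 0.02 | 3.3–6.1% | 4.1–5.1% |
| 0.05 | 6.0–10.2% | 3.7–5.0% |
| 0.10 | 10.3–16.5% | 2.6–4.8% |

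**Step 3: two variants that the protocol leaves open.**

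- After 20% loss, 14 × 0.8 = 11.2, so about 11 students per school remain. Fisher's error is then about 4–8% at ICC 0.05 and 7–14% at ICC 0.10.
- If the 12 schools in Section 3.8 are the total, there are 6 per arm, and 140 / 6 = 23.3 gives about 23 students each. Fisher's error is then about 9–15% at ICC 0.05 and 16–24% at ICC 0.10.

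The school-level t test stays at or below about 5% in both variants.

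**The case against.** **School is a random factor for each outcome measure.** That sentence follows the linear mixed model and describes it. Fisher's test has no random effect, and the protocol assigns attempts to it separately. This does not answer the point.

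**The detail belongs in the analysis plan.** It would if the protocol were silent. Here it names a specific test that does not match the design.

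**The error may not be inflated at all.** This stands in part. Fisher's conservatism absorbs mild clustering: with 10 × 14 per arm the error stays below 5% at an ICC of 0.01 or less, and at 0.02 when the risk is 3% to 5%. A low ICC is a live possibility. Assuming 80% power and an effect of 0.4 SD, 99 students per arm × 1.13 = 112, and 112 / 0.8 = 140, so the planned size can be matched with an ICC of 0.01. That is an inference about the primary score, not a stated value, and the ICC for attempts could differ. Nor is conservatism that happens to offset clustering a safeguard, because the test cannot adapt to whatever correlation occurs.

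**The mechanism is only half documented.** This also stands. Section 3.2.1 gives one psychologist per school for delivery of the experimental programme. That is a reason to expect correlation in intervention schools, not a documented one for control schools.

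**The outcome is secondary.** True. It does not appear in the hypotheses of Section 1.2, and the primary analysis models school.

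**Conclusion.** The named test does not fit the randomisation and departs from the protocol's own treatment of school. At any positive ICC its p-value is smaller than the clustering warrants. Whether the actual error exceeds 5% depends on the ICC and the attempt risk, neither of which the protocol gives. In the planned 10 × 14 design the error passes 5% at every risk tried once the ICC reaches 0.05 (about 6–10%), and is about 10–17% at 0.10.

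A reader might infer that the p-value will be materially too small whatever happens. The documents do not support that: with weak clustering and few events the test stays within its level. A reader might also infer that the trial's main conclusion is at risk. It is not, because the ideation analysis includes school. Nor should error rates be quoted for six schools of 14 per arm: that is 84 students against the stated 140, a design the protocol does not describe.

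This should be fixed, but it does not threaten the primary result.

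**What to change.** In Section 7.1, replace Fisher's test with one prespecified analysis that respects schools. A permutation test or a t test on school-level attempt proportions would do. If permutation is chosen, re-randomise schools only among allocations that satisfy the balancing on school size and vulnerability index described in Section 4. Report the risk difference with a cluster-adjusted confidence interval.

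A mixed logistic model with school as a random intercept and a small-sample correction can be supportive. State now which analysis is primary for this outcome, and do not let the number of events seen in the data decide the method.

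The cost is a sentence or two, with no new data, visits or participants. The interval will be somewhat wider. The change should be made before the group codes are opened to the analyst.
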